## Abstract

**Introduction:**

Adequate nutrition during pregnancy is crucial to both mother and child. Maternal malnutrition can be the cause of stillbirth or lead to poor birth outcomes such as preterm delivery and small-for-gestational-age newborns. There is a probable positive effect of providing pregnant women a balanced energy-protein (BEP) food supplement, but more evidence is needed. The MIcronutriments pour la SAnté de la Mère et de l’Enfant (MISAME) III project aims to improve birth outcomes and infant growth by testing a BEP supplement during pregnancy and lactation in rural Burkina Faso. This paper describes the study protocol.

**Methods and analysis:**

MISAME-III is a four-arm individually randomised efficacy trial implemented in six rural health centre catchments areas in the district of Houndé. Eligible pregnant women, aged between 15 and 40 years old and living in the study areas, will be enrolled. Women will be randomly assigned to one of the four study groups: (1) prenatal intervention only, (2) postnatal intervention only, (3) prenatal and postnatal intervention or (4) no prenatal or postnatal intervention. The intervention group will receive the BEP supplement and iron/folic acid (IFA) tablets, while the control group will only receive the IFA tablets following the national health protocol. Consumption will be supervised by trained village women on a daily basis by means of home visits. The primary outcomes are small-for-gestational age at birth and length-for-age z-score at 6 months of age. Secondary outcomes will be measured at birth and during the first 6 months of the infants’ life. Women will be enrolled from October 2019 until the total sample size is reached.

**Ethics and dissemination:**

MISAME-III has been reviewed and approved by the University Hospital of Ghent and the ethics committee of Centre Muraz, Burkina Faso. Informed consent will be obtained. Results will be published in relevant journals and shared with other researchers and public health institutions.

**Trial registration number:**

NCT03533712.

Strengths and limitations of this studyThis trial will help to fill the evidence gap on the effect of balanced energy-protein (BEP) supplements in pregnant and lactating women on birth outcomes and infant growth.Formative research to select the most suitable BEP supplement ensured that the selected BEP is well accepted by the study population.The daily intake of BEP supplements and iron/folic acid tablets during pregnancy and lactation will be directly observed by study workers.This study will assess the impact of factorial combinations of prenatal and postnatal BEP on child growth to elucidate the relative importance of BEP during pregnancy and/or early lactation.Blinding of study participants and staff members will not be possible, as the supplements are identifiable.

## Introduction

Pregnancy is a challenging period in the life of many women in low-income and middle-income countries (LMICs). Maternal mortality remains high, and many neonates suffer from premature delivery and/or intrauterine growth retardation, both in length and in weight accumulation.^1^ An indicator to measure neonatal growth is small-for-gestational age (SGA). SGA is defined as a birth weight below the 10th percentile of a standard optimal reference population for a given gestational age and sex.^2^ SGA is often caused by growth restriction in the womb and has been associated with neonatal and postneonatal mortality.^2^ It has also been linked to an increased risk of morbidity later in life, especially non-communicable diseases.^3^ SGA affected 23.3 million term children in LMICs in 2012.^4^ Adequate nutrition during pregnancy is crucial for optimal maternal and newborn health,^5 6^ and maternal malnutrition has been associated with fetal growth restriction.^7^ An adequate dietary balance is necessary to ensure sufficient energy intake for adequate growth of the fetus.^8^ Unfortunately, maternal undernutrition remains a public health challenge in regions across sub-Saharan Africa and Asia.^9 10^

Several types of food supplements have been developed and evaluated over the past years. A positive effect of multiple micronutrient supplements (MMS) during pregnancy on birth outcomes has been found in previous studies.^11^ Keats *et al*^11^ concluded in their review that MMS during pregnancy gave a probable reduction in SGA and preterm births and can thus be used for future guidance. According to a multicountry randomised controlled trial (RCT) done in LMICs, a positive effect of lipid-based nutrient supplements on fetal growth-related birth outcomes can be seen when starting supplementation before conception or during the first trimester.^12^ Moreover, the latest evidence indicates a possible positive effect of providing pregnant women a balanced energyprotein (BEP) food supplement.^5 13–15^ In line with that evidence, the 2016 WHO’s antenatal care guidelines state that pregnant women in undernourished populations should receive, depending on the context, BEP supplements to reduce the risk of stillbirth and SGA.^6^ Researchers, however, still highlight the limited amount of evidence and a need to evaluate the effect of balanced supplements on birth outcomes, such as SGA.^5 13^ Experimental trials of high-quality and large sample sizes, especially in undernourished pregnant women, are thus needed.^13^ Following this recommendation, compositional guidance for a ready-to-use food supplement for pregnant women was developed by the Bill and Melinda Gates Foundation (BMGF) in 2016.^16^

Two previous projects, MIcronutriments pour la SAnté de la Mère et de l’Enfant (MISAME) I and II, conducted in Burkina Faso, investigated the effect of supplementation during pregnancy and the effect on birth outcomes in infants.^17 18^ MISAME-I compared the effect of the UNICEF/WHO/UNU international multiple micronutrient preparation (UNIMMAP) with the effect of iron/folic acid (IFA) alone on fetal growth in a double-blind RCT and concluded that UNIMMAP modestly but significantly increased fetal growth.^17^ The second study (MISAME-II) assessed the effect of a lipid-based nutrient supplement fortified with UNIMMAP compared with a UNIMMAP tablet during pregnancy in an open-label, individually randomised controlled trial on birth anthropometry. It was found that combining energy with micronutrients during the prenatal phase led to larger birth lengths.^18^ Since MISAME-II used the UNIMMAP as a control, a complete assessment of the impact of the fortified lipid-based UNIMMAP was not possible. Therefore, MISAME-III will study the effect of a BEP supplementation, compared with a control group, and extend the supplementation postnatally to investigate the net contribution of prenatal and postnatal BEP supplementation on child linear growth up to 6 months of age.

In summary, the MISAME-III study hypothesises that: (1) providing women with a BEP supplement during pregnancy will decrease the incidence of SGA compared with the control group; and (2) providing them with a BEP supplement during the postnatal period will increase children’s length by the age of 6 months compared with the control group.

## Methods

This protocol has been developed in accordance with the Standard Protocol Items: Recommendations for Interventional Trials guidelines (online supplemental file 1).

10.1136/bmjopen-2020-038393.supp1Supplementary data

### MISAME-III study design

The MISAME-III project is an individually randomised 2×2 factorial efficacy trial aiming to improve birth outcomes and infant growth in rural Burkina Faso by testing a BEP supplement during pregnancy and lactation (figure 1). At inclusion, pregnant women will be individually and randomly allocated to a prenatal intervention or control group and a postnatal intervention or control group. The intervention group will receive a daily BEP supplement to be consumed under supervision for the duration of pregnancy/lactation. Both intervention and control groups will receive the standard IFA tablet through the national antenatal care. In addition to the main trial, we propose a number of substudies to test specific hypotheses in a subsample of pregnant/lactating women and children. MISAME-III began with a formative study to identify the preferred product type for the provision of a fortified BEP supplement during the RCT.

**Figure 1 F1:**
[figure not shown]
Study design of the randomised controlled trial.

### Study setting

The study will be conducted in the district of Houndé in Burkina Faso, a landlocked country situated in West-Africa; similar to the previous MISAME studies, Burkina Faso has an infant mortality rate of 53 per 1.000 live births,^19^ with an estimated Low Birth Weight (LBW) prevalence at 14% in 2013.^20^ The prevalence of SGA has been estimated to be between 32.2% and 41.6% in the district of Houndé.^17^ The Demographic and Health Survey of 2010 reported that 16% of women had a body mass index (BMI) below 18.5 kg/m^2^, which indicates the presence of chronic energy deficiencies in the zone.^21^ The highest prevalence can be found in the Eastern region, where 31% of women have a BMI lower than 18.5 kg/m², that is, low BMI.^22^ Moreover, in particular, adolescent Burkinabèe girls between the age of 15 and 19 years have a low BMI, with an estimated prevalence of 23%.^23^ Micronutrient deficiencies also remain a major problem in both infants and women of reproductive age in the country.^23 24^

The climate of the country is Sudano-Sahelian, with a dry season from October to March/April and a rainy season from May until September/October. The diet is essentially cereal based^25^ with maize as the main staple food.^26^

MISAME-III will be conducted in the same health district where the two previous MISAME studies were organised. The study villages are concentrated around six health centres, which are within an accessible range from the district hospital. A list of all study sites can be found on: www.misame3.ugent.be

### Study population and recruitment

Women living in the study villages and aged between 15 and 40 years will be identified through a census. The villages were selected based on their accessibility and distance to the nearest health centre, number of facility-based deliveries per year and their agricultural model as some households tend to reside on their fields during the harvest season. Trained village women (femme accompagnante (FA)), selected in collaboration with the community leaders, will visit the households every 5 weeks to ask about women’s menstruation. In case of amenorrhoea, women will be sent to the nearest health centre for a pregnancy test and a first antenatal consultation by our project midwife when tested positive. An ultrasound examination will be completed soon after inclusion by the project medical doctor to assess gestational age. A baseline interview will also be done by the project interviewers to assess the household members’ characteristics, household properties, water sanitation and hygiene (WASH) and household food security.

Inclusion criteria:

Women between 15 and 40 years old at study inclusion.Confirmed pregnancy by a pregnancy test and ultrasound.Women who signed the informed consent form.

Exclusion criteria:

Pregnancies >20 weeks of gestational age.Women planning on leaving the area during their pregnancy.Women planning on delivering outside the study area.Women who are allergic to peanuts.Women with multifetal gestations (exclusion from analysis).

FAs will be informed by the project midwife when a participant has been included. FAs will visit pregnant women on a daily basis to distribute the BEP supplement and/or IFA tablet and to supervise consumption. During the postnatal period, FAs will distribute the supplements and IFA tablets to the intervention group on a daily basis until 6 weeks after birth. From that moment onwards, they will receive a week’s worth of BEP supplements. The postnatal control group will receive the IFA tablets on a daily basis during the first 6 weeks after birth, and participants will thereafter be visited once a week (without any supplementation) to minimise the effect of home visits. The FA will inform women on the supplement’s function, the importance of antenatal visits during pregnancy, maintaining a healthy diversified diet, the importance of delivering at a health facility, the importance of exclusive breast feeding and the introduction of complementary foods at the age of 6 months. Throughout the study, the FAs will be supervised by project interviewers. Supervision visits will be conducted using Lot Quality Assurance Sampling schemes and empty sachet counts to ensure that study participant are visited according to the project protocol.

### Manufacturing of 12 fortified BEP supplements and the formative study

Twelve fortified BEP supplements were pretested before the start of the RCT during a formative research phase. Several food manufacturing companies were invited to produce ready-to-use BEP supplements following the compositional guidelines proposed during an expert meeting hosted by the BMGF^16^ in September 2016 (table 1). The BEP supplements had to be: (1) ready to consume, (2) not need a cold chain and (3) microbiologically stable.

**Table 1 T1:** The compositional guidelines for macronutrients and micronutrients

Nutrition component	Target per serving
Total energy	250–500 kcal per serving.
Fat content	10%–60% of energy intake.
Protein content	16 g (14–18 g) with a digestible indispensable amino acid score of ≥0.9.
Carbohydrates	Between 45 g and 32 g per 100 g (added sucrose between 20 g and 10 g per 100 g).
Trans fats	<1% of energy intake.
Fatty acid	(Optional): min of 1.3 g of n-3 or 300 mg docosahexaenoic acid (DHA)+eicosapentaenoic acid (of which 200 mg DHA) to achieve a healthy n-6: ratio of the supplement of 5:1.
Micronutrients	Vitamin A, D, E, K, B1 (thiamin), B2 (riboflavin), B3 (niacin), B6 (pyridoxine), B9 (folate), B12 and C; minerals: iron, zinc, iodine, calcium, phosphorous, copper and selenium.
Optionally	Pantothenic acid, manganese, potassium, biotin and choline will be included.
	The final composition of the product will be determined by the selected product as the manufacturing process will influence the macronutrient composition.

Seven out of 12 supplements were characterised as sweet and five as savoury. Products were produced in different forms, including a biscuit, pillow, wafer, bar, paste, instant drink and soup.

In a first screening step of the formative study, the two most preferred BEP supplements were identified by using a combined evaluation approach consisting of a single meal test, sensory evaluation and focus group discussions, in a convenience sample of 40 pregnant women. In a next step, we compared the acceptability of the two preselected BEP supplements using a 10-week home-feeding study, with 80 pregnant women, to select to most preferred product for the RCT. We refer to both papers for detailed information.^27 28^

### Study intervention

At inclusion, pregnant women will be randomly allocated to four different study groups: (1) prenatal intervention only, (2) postnatal intervention only, (3) prenatal and postnatal intervention or (4) no prenatal and no postnatal intervention. Prenatal and postnatal supplementation will start right after inclusion and birth, respectively. The prenatal intervention group will receive the BEP supplement and IFA, while the control group will receive IFA tablets alone. The IFA tablets contain 65 mg iron and 0.4 mg folic acid. The postnatal intervention group will receive the BEP supplement for 6 months in combination with the IFA tablets for 6 weeks following the national protocol of Burkina Faso; the control group will receive IFA alone for 6 weeks.

### Allocation/randomisation

We will apply a stratified permuted block randomisation schedule to allocate women to the prenatal intervention or control group and in a next step to allocate women to a postnatal intervention and control group. Per health centre (ie, stratum), women will be individually randomly in permuted blocks of 8 so that, per block, equal numbers are obtained in the prenatal intervention (n=4) and control (n=4) group and equal numbers are also obtained in the postnatal intervention (n=4) and control (n=4) group. The double random sequence will be generated before the start of the study using Stata V.15.1 (Statacorp, Texas, USA) by an external research analyst. The allocation group will be coded with two letters (A or B for the prenatal and Y or Z for the postnatal study group) and placed in a sequentially numbered sealed opaque envelopes by project employees, not in direct contact with participants. At study enrolment, the project midwife will draw the next sealed envelope and allocate the participant to the study group defined by the letter code in the envelope. Blinding of participants and community-based project workers will not be possible since the supplements are identifiable. Field staff responsible for measuring primary and secondary study outcomes are not directly involved in the daily supplementation of the study participants and can therefore be considered to be partially blinded.

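### A fixed block size of 8 per health centre in an open-label trial could let the enrolling midwife deduce up to one in five prenatal allocations in advance

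*Protocol article*

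**What the plan says.** All of the randomisation rules are in the protocol article under Allocation/randomisation.

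- **Stratum.** The schedule is applied "Per health centre (ie, stratum"). Study setting gives the number of strata: "The study villages are concentrated around six health centres".
- **Block.** Within a centre, "women will be individually randomly in permuted blocks of 8 so that, per block, equal numbers are obtained in the prenatal intervention (n=4"), with four in the prenatal control group. For the other factor, "equal numbers are also obtained in the postnatal intervention (n=4) and control (n=4) group". No variation in block size is described.
- **Who sees the code.** Once a woman is included, "the project midwife will draw the next sealed envelope and allocate the participant to the study group defined by the letter code". The code has one constant letter per arm: A or B for prenatal, Y or Z for postnatal.
- **Blinding.** "Blinding of participants and community-based project workers will not be possible since the supplements are identifiable".
- **Safeguards.** An external analyst generates the sequence before the study starts. The envelopes are opaque, sealed and sequentially numbered, and are filled by employees who do not deal directly with participants.

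Under Ethics approval and consent to participate, project midwives also explain the trial to eligible women. Under Study population and recruitment, they carry out the first antenatal consultation.

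**The concern.** Allocation concealment has two parts: nobody should be able to read the next assignment, and nobody should be able to work it out. The envelopes deal with the first. The second depends on the block structure, and here every block has the same size and an exact 4:4 split, the stratum is a single centre, and the same role sees each code and speaks to the next woman. The supplements are identifiable, so the meaning of the letters soon becomes plain. Once four of one prenatal letter have appeared in a block, the remaining assignments in it are determined.

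Someone who foresees an assignment has some room to act on it. Two exclusion criteria rest on a woman's stated plans (leaving the area, delivering elsewhere), and the consent conversation and the timing of the first visit are flexible. If women entering foreseeable slots differed between arms in their risk of a small newborn, the prenatal comparison of SGA would be biased, and the postnatal comparison of LAZ could be affected in the same way through its own letter. Partial blinding of outcome assessors does not protect against this, because the bias arises at entry. A larger sample does not remove it either.

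**Working it through.** **Inputs.** Block of 8, 4:4 on the prenatal letter, stratum = health centre (Allocation/randomisation); six centres (Study setting); 888 per prenatal arm, 1776 in total, SGA 32% with an anticipated decrease of 7% (Sample size). The article gives no predictability figure.

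**The plan's own figures.** Two proportions, 0.32 against 0.25, two-sided α = 0.05, power 0.80, no continuity correction:

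n = [1.960·√(2·0.285·0.715) + 0.842·√(0.32·0.68 + 0.25·0.75)]² / 0.07² = 652 per arm, as stated.

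The decrease is therefore 7 percentage points. The total is 2 × 888 = 1776 = 222 blocks of 8. The sample size does not depend on the block size.

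**Assignments known with certainty, fixed block of 8.** Assume an observer who knows the block size, knows where each block starts and has seen every earlier draw at the centre. There are C(8,4) = 70 equally likely orderings. Counting the positions that come after one letter is used up:

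| Position in block | 1–4 | 5 | 6 | 7 | 8 |
|---|---|---|---|---|---|
| Share of blocks in which it is certain | 0 | 2.9% | 14.3% | 42.9% | 100% |

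The sum is 112/70 = 1.6 per block. The closed form for a block of 2m agrees: 2m/(m+1) = 8/5 = 1.6. As a share this is 1.6/8 = 20.0%, and 0.20 × 1776 ≈ 355 women.

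**Best guess.** Always guessing the letter used less often so far in the block is right 66.6% of the time, against 50% by chance.

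**Varying, undisclosed sizes.** This was simulated for an observer who knows the set of possible sizes but not the size of the current block. Sizes are drawn with equal probability, with 296 women per centre (1776/6, equal centres assumed) and 3000 repetitions:

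| Block sizes | Certain in advance | Women of 1776 | Best guess correct |
|---|---|---|---|
| 8 fixed | 20.0% | about 355 | 66.6% |
| 4, 8 | 7.5% | about 134 | 68.0% |
| 4, 8, 12 | 2.8% | about 50 | 66.1% |
| 8, 12, 16 | 1.6% | about 29 | 64.0% |

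Varying the size removes most of the certainty but little of the guessing advantage. Requiring two women per combination in a fixed block of 8 would leave prenatal predictability at 20%.

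**Illustrative size of bias (assumption, not in the document).** If women in foreseeable control and intervention slots differed in SGA risk by d points, the prenatal contrast would shift by 0.20·d. For d = 5 to 10 this is 1 to 2 points, or 1/7 = 14% to 2/7 = 29% of the 7-point effect. Since 20% is an upper bound, so is this shift for a given d.

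**The case against.** **The 20% is conditional.** The article does not say that midwives are told the block size, or how many midwives draw envelopes at each centre. A reader might infer from publication of the size that field staff knew it during recruitment; the document does not show that. This objection stands: 20% and 355 women are upper bounds, and the share is lower if draws are split between people who do not share them. It does not remove the point, because with constant letters and a tally that evens out every eighth draw, staff could infer the size.

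**The route to selection is narrow.** Women are found through a census and five-weekly home visits and are then referred to the health centre, so the midwife does not choose whom to approach. Household food security is collected by interviewers at a visit that Table 3 places after allocation, so she does not have it when drawing. Both facts limit the opportunity. What remains is what she can see at the first consultation, such as thinness, together with the consent conversation and the exclusions that rest on stated plans. A reader might infer that selection took place; nothing in the document supports that.

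**The four groups.** A reader might also infer that blocks are unbalanced across the four prenatal–postnatal combinations. The article guarantees only 4:4 on each factor, with the second letter assigned "in a next step to allocate women to a postnatal intervention and control group", and neither states nor excludes two women per combination. If the factors were permuted independently (an assumption), 36/70 = 51% of blocks would be 2:2:2:2, and each group would average 444 with SD √(222 × 4/7) = 11.3. That is a negligible loss of precision. The 294 per combination under Sample size is a power figure for children analysed after losses, not an allocation rule. This is not a separate finding.

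**Guessing.** The 66.6% hit rate cannot be used to argue for varying the block size, because that change hardly moves it and sizes of 4 and 8 alone raise it slightly.

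**Conclusion.** The concern holds as a weakness of concealment, not as evidence of bias. The stated rule makes up to 20% of prenatal allocations, at most about 355 of 1776, deducible by a midwife who knows or infers the block size and has seen all earlier draws at her centre. The envelopes and the external analyst do not prevent that deduction. Selective enrolment or timing is thus possible and could bias SGA and LAZ; whether it occurred, and by how much, cannot be read from the document. The percentage is exact under those conditions and lower if any of them fails. The change is worth making because it addresses a stated rule, costs little and removes most of the certainty. It should not be presented as making assignments unguessable.

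**What to change.** For envelopes not yet used, have the external analyst generate a new list per health centre with randomly varying block sizes that are multiples of 4, for example 8, 12 and 16, or 4, 8 and 12. Do not disclose the sizes to field staff or to those who could pass them on. The first set leaves less certainty and slightly lower guessing accuracy; the second keeps tighter balance within a centre. The new list can also permute AY, AZ, BY and BZ equally within each block at no extra effort, as a minor by-product.

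The cost is more than a program run. Unused envelopes at six centres must be recalled and replaced, the current part-used blocks stay incomplete, the change has to be recorded as a protocol change, and the possible imbalance per centre at the end of the list is slightly larger. Sample size is unaffected.

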### Sample size

With an SGA prevalence of 32% and an anticipated decrease of 7%, a sample of 652 subjects per prenatal arm is required with α=0.05 and β=0.2.^26^ To accommodate for possible losses, the number of subjects per arm was increased to 888 (total subjects: 1776). Possible losses are based on previous MISAME studies where the prevalence was ~26 % due to a combination of miscarriage, stillbirths, multifetal pregnancies, outmigrants, maternal deaths and incomplete data.^18^ For the analysis of an effect of the postnatal intervention on LAZ at 6 months of age, the minimally detectable effect depends on the presence or absence of an interaction effect between the prenatal and postnatal intervention. In the absence of a statistically significant interaction between prenatal and postnatal intervention, at sample size of 588 children per postnatal study arm would allow us to detect a difference of 0.18 Z-score (SD=1.1) based on a cross-sectional survey conducted in the Gourcy health district in Burkina Faso,^31^ between study arms with α=0.05 and β=0.20. This implies that if ~1400 singleton live births are available, we allow for a maximum loss to follow-up of 16%. In the presence of a statistically significant interaction between prenatal and postnatal intervention, a total sample size of 1176 represents 294 children per factorial combination of the prenatal and postnatal study group (four groups in total). A subgroup size of 294 would allow us to detect a difference in LAZ at 6 months of age of 0.28 assuming an SD of 1.1, α=0.025 (Bonferroni correction for two primary endpoints analyses) and β=0.20.

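### The postnatal letter is opened at enrolment, well before it is needed, so loss before birth could differ by postnatal arm and bias the 6-month LAZ comparison

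*Protocol article*

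**What the plan says.** Both factors are allocated at the same moment. Under MISAME-III study design: "At inclusion, pregnant women will be individually and randomly allocated to a prenatal intervention or control group and a postnatal intervention or control group". Under Study intervention: "At inclusion, pregnant women will be randomly allocated to four different study groups".

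Allocation/randomisation describes the mechanics. The group is "coded with two letters (A or B for the prenatal and Y or Z for the postnatal study group"), and the code is placed in sequentially numbered sealed opaque envelopes. Then: "At study enrolment, the project midwife will draw the next sealed envelope and allocate the participant to the study group defined by the letter code". The same section states: "Blinding of participants and community-based project workers will not be possible since the supplements are identifiable".

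The two interventions begin at different times: "Prenatal and postnatal supplementation will start right after inclusion and birth, respectively" (Study intervention). The exclusion criteria include "Pregnancies >20 weeks of gestational age" (Study population and recruitment), so enrolment falls in the first half of pregnancy.

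No section says that the postnatal letter is withheld until delivery. No section says that the woman is told her postnatal group at enrolment either.

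**The concern.** LAZ at 6 months is the primary outcome for the postnatal intervention, and it exists only for children whose mothers are still in the study. If the postnatal letter is known during pregnancy, staying in the area or in the trial can depend on whether food is expected after birth. The live births entering the LAZ comparison would then have been partly selected by arm, and analysing them by allocated group cannot recover children who were never measured.

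The letters are codes, but that protects little. Each factor has one fixed pair of letters, so the meaning of Y and Z can be worked out in a health centre once the first deliveries there lead to visible supplements or to none. The project midwife who opens the code is also a main trial contact: she gives the first antenatal consultation, explains the complete trial at consent and administers the depression questionnaire.

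The protocol itself treats mobility as a threat. Loss to follow-up is defined as moving away or withdrawing (Data collection), and the Discussion says that women leaving to work on distant fields disrupted supplementation in earlier trials.

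**Working it through.** **Inputs from the protocol article, Sample size.** 888 women per prenatal arm, 1776 in total; about 1400 singleton live births; 588 children per postnatal arm; difference 0.18 z; SD 1.1; α = 0.05; power 0.80; at most 16% loss after birth. The blocks of 8 balance the postnatal letter, so about 888 women are also enrolled per postnatal arm.

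**The plan's own figures reproduce.**
- LAZ sample size: n = 2(1.960 + 0.842)² × 1.1² / 0.18² = 587 per arm, against 588 stated. Power at 588 is 80.1%.
- Loss after birth: 1 − (2 × 588)/1400 = 1 − 1176/1400 = 16.0%, as stated.

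**Time between opening and use.** Taking a term birth as about 40 weeks (an assumption), 40 − 20 = 20 weeks at the latest permitted entry, and longer for earlier entry.

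**Implied loss between enrolment and the LAZ starting cohort.** 1 − 1400/1776 = 21.2%, or 376 women. The share due to out-migration, withdrawal or missed follow-up is not given.

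**Size of the possible bias.** Let e be the excess proportion lost before birth in one postnatal arm, and g the LAZ gap between the children of those extra women and the other children. Neither value is in the documents. With average retention 0.788, the arm that keeps the extra women retains 0.788 + e/2, and its mean moves by

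shift = g × e / (0.788 + e/2).

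For e = 0.05 and g = 0.5: 0.025 / 0.813 = 0.031 z. This corresponds to 18.7% against 23.7% lost, or 0.05 × 888 ≈ 44 more women lost in one arm.

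The standard error of the LAZ contrast at the planned size is 1.1 × √(2/588) = 0.064.

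| Excess loss e | Shift, g = 0.25 | Shift, g = 0.5 | Shift, g = 1.0 | g = 0.5: share of 0.18 | g = 0.5: type I error |
|---|---|---|---|---|---|
| 0 | 0 | 0 | 0 | 0% | 5.0% |
| 2 points | 0.006 | 0.013 | 0.025 | 7% | 5.4% |
| 5 points | 0.015 | 0.031 | 0.062 | 17% | 7.7% |
| 10 points | 0.030 | 0.060 | 0.119 | 33% | 15% |

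The direction depends on which arm loses more and on whether the lost children would have been shorter or longer. If the shift works against the intervention, power for a true 0.18 at g = 0.5 falls from 80.1% to about 74%, 64% and 47% at 2, 5 and 10 points.

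**After the change.** Withholding the letter until birth alters no sample size: about 700 live births per postnatal arm, 588 after 16% loss, power 80.1%. Loss before birth could then no longer depend on knowledge of the postnatal letter.

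**The case against.** Allocating both factors at enrolment is a legitimate factorial design, and no section contradicts another. The protocol also limits the risk: women planning to leave or to deliver elsewhere are excluded, all women are visited daily in pregnancy, and reasons for discontinuation are recorded. All of this stands. It makes the point an avoidable weakness rather than an error, but none of it prevents arm-dependent loss.

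Three stronger readings are tempting and are not supported.

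- *A reader might infer that each woman is told her postnatal group at enrolment.* The text establishes only that the midwife opens a letter code. The reason given for the lack of blinding is that supplements are identifiable, and no postnatal supplement is in use before birth. What the woman is told may be set out in the consent form, which is not shown.
- *A reader might treat all loss before birth as exposed, or put it as high as the planned 26%.* The 26% is an all-cause figure that includes incomplete data, so it is not a count of losses before birth. Within the 21%, multifetal pregnancies are excluded by rule, and miscarriage, stillbirth and maternal death have no credible route from a supplement expected later. The 21% is also only implied, since the figure of 1400 births is stated conditionally.
- *A reader might extend the concern to SGA.* SGA assesses the prenatal intervention. The postnatal letter is randomised and balanced, so expecting postnatal food should be spread alike over the prenatal arms. Bias there would need an interaction with prenatal arm, which nothing in the text suggests.

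It is also fair to say that the bias is modest in the middle of the range: 0.031 z is about half a standard error.

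**Conclusion.** The point holds as an avoidable risk to one primary comparison. The early opening of the postnatal letter is stated in the text; that it leads to differential loss is possible but not shown. With no differential loss the bias is zero. At a 0.5 z gap it is 0.013 z for 2 points of excess loss, 0.03 z for 5 and 0.06 z for 10, against the 0.18 z target. It becomes material only if the excess reaches about 5 points and the lost children differ clearly in LAZ. Both inputs are assumptions, and the documents give nothing to narrow them. The loss after birth, for which the plan allows up to 16%, occurs when the supplement is visible and remains exposed whatever is done here. The change is worth making because it is cheap, not because a large bias has been demonstrated.

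**What to change.** Keep the pre-generated double sequence. Place only the prenatal letter in the enrolment envelope, and put the postnatal letter in a second sealed opaque envelope carrying the woman's study number, to be opened at confirmed live birth. Opening at that moment keeps the stated start of postnatal supplementation. Waiting for the birth measurements would not, because these may take up to 72 hours.

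Define the LAZ analysis population as all live-born singletons by their randomised postnatal letter, whether or not the envelope was opened on time, so that inclusion does not depend on staff action. Report losses before birth, with reasons, by postnatal arm.

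If enrolment is too far advanced to change the envelopes, state who knew the postnatal letter during pregnancy and whether women were told, and still report those losses by postnatal arm.

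The cost is one more envelope per woman and a field procedure that ensures prompt opening at delivery. Sample size and power do not change.
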